## **IV.3 - REQUIRED NUMBER OF SUBJECTS**

A total of 150 patients are planned to be enrolled in the experimental group (multidisciplinary programme) and 150 patients in the control group, i.e. 300 patients in total.

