## **VIII.2 - TRANSCRIPTION OF INFORMATION INTO THE CASE REPORT FORM**

The study data will be collected using the CleanWeb electronic case report form, within the framework of a public contract between the AP-HP and TELEMEDICINE TECHNOLOGIES S.A., notified on 17/11/2003 (reference no. 033845) and renewed on 26/11/2006 (reference no. 063844). The data will be centralised in a server located at the Operational Services Department (DSO) of AP-HP, [name].

An initial version of the eCRF may be put online and tested after sending the specific study specifications by fax to the company TELEMEDICINE. Once the Coordinator, the Project Leader, the Clinical Research Unit, the Data Manager and the Statistician have agreed on the final version of the eCRF, and following the release of the credits, and submission of the purchase order to the company TELEMEDICINE by the DRCI, the eCRF will come into operation.

In accordance with the Good Clinical Practice guidelines, the case report form in which the study data are transcribed must correspond to at least the following standard presentation:

- At the start of the form, the following are normally included: the title of the study, the patient's study reference, possibly the contact information of the individual taking part in the study (first initials of their surname and first name), randomisation number (where applicable), and inclusion and exclusion criteria in the form of a check-list, which allows subject selection to be validated with respect to the study population. At the end of the study, when the study database has been “frozen”, the eCRFs of each patient will be printed and signed by the investigator. The references of the study and of the person taking part in the study will then appear in the form of a slip on each page to allow data to be identified in all cases.
- The visit and/or sampling dates of the data transcribed must be reported in this eCRF as well as the point in the study to which they correspond.
- Results must contain the units of measurement, and even the laboratory standards in the event that these vary with the technique used.
- The following items must be included at the end of the eCRF:
  - Concomitant treatments;

- Non-serious adverse events (AEs);
- End of study/Early termination;
- Outside planning, an SAE module.

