## **X - SAFETY ASSESSMENT**

### **X.1 - DEFINITIONS**

According to Article R1123-39 of the French Public Health Code:

- **Adverse event:**

Any harmful manifestation occurring in an individual taking part in a biomedical research study, regardless of whether or not the manifestation is related to the study.

- **Adverse event** in a study not involving a product mentioned in Article L.5311-1 (medicinal products, biomaterials and medical devices, in vitro diagnostic medical devices, labile blood products, organs, tissues, cells and products of human or animal origin, and cellular products for therapeutic purposes).

Any adverse event due to the study.

- **Serious adverse event or effect:**

Any adverse event or effect that leads to death, is life-threatening for the individual taking part in the study, involves hospital admission or an extended hospital stay, causes significant or permanent incapacity or disability, or leads to a congenital abnormality or malformation.

- **New information:**

Any new safety information that may lead to a reassessment of the risk-benefit ratio of the study, or which may be enough to consider making amendments to study-related documents, to the way the study is conducted and, where applicable, to the way the product is used.

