### **X.3 - SERIOUS ADVERSE EVENT MANAGEMENT PROCEDURE**

The adverse event reporting table will be included as an annex to the protocol. It will include:

- the list of SAEs which do not have to be reported to the sponsor: anything related to the usual natural course of knee osteoarthritis (worsening of the condition, elective and non-elective admission to monitor the condition); any serious adverse event which may be related to treatments prescribed as part of care during the study follow-up period; any other medical event apart from knee osteoarthritis, not related to the additional procedures required for this study;
- The list of AEs expected during the study;
- The reference to "none", in the column of serious adverse events expected during the study.

Only SAEs directly related to the additional procedures required for this study are to be reported to the sponsor immediately, from the day on which the investigator becomes aware of them.

In the event that the investigator becomes aware of an event that could affect the safety of any individual involved in the study (e.g., therapeutic error or protocol deviation), he or she will be required to report this to the sponsor using the form provided for this purpose and attached as an annex to the protocol.

The investigator will fill in the serious adverse event report form (from the study case report form) (see annex) and send it to the DRCI Vigilance Unit by fax to ([contact] 99 (if

possible, after immediately calling ([contact] 23 in the event of unexpected death or a life-threatening event).

For each serious adverse event, the investigator must issue an opinion regarding the causal relationship of the event with any additional procedures specifically required for the study.

Obtaining information regarding the description and evaluation of an adverse event may not be possible within the time limit for the initial reporting. Furthermore, the clinical course and results of any clinical work-ups and diagnostic and/or laboratory studies, or any other information enabling a proper analysis of the causal relationship, will be reported:

either with the initial SAE report if they are immediately available;

or at a later date, as soon as possible, by sending a new SAE report form by fax (specifying that this is a follow-up to a previously reported SAE and providing the follow-up number).

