## **4 Principles of analysis**

### **4.1 General principles for the endpoint analysis**

The results will be reported in line with the CONSORT 2010 recommendations.

The endpoint analysis will be carried out in the ITT population.

The statistical analysis will be carried out with blinding in terms of the randomisation group.

No interim analysis is planned for this trial.

All the endpoints will be tested for superiority.

As the analyses are based on modelling or other numerical approaches, they require verification of the underlying hypotheses as well as convergence of their algorithms. If these conditions are not verified, an alternative method will be used.

The analyses will be carried out using R software version 3.4.4 or later (The R Foundation for Statistical Computing, Vienna, Austria).

The tests used will be bilateral with a significance threshold of 2.5% for the two primary endpoints and 5% for the secondary endpoints. The 2.5% threshold was chosen to take into account the double primary endpoint.

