#### **7.1.2 Analysis**

Adverse events and their characteristics will be described in the form of sample sizes and percentages by treatment arm. Fisher's exact tests will be used to compare the two treatment arms in terms of the proportion of patients with at least one AE/SAE and the proportion of patients with at least one SAE. The total number of AEs/SAEs and SAEs will also be described for each arm.

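### The plan tests SAEs between arms but does not ensure that serious events of any cause are recorded, and identifiable as serious, in both arms

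*Supplement*

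**What the plan says.** **The analysis.** SAP 7.1.2 describes adverse events by arm and applies Fisher's exact test to "the proportion of patients with at least one AE/SAE and the proportion of patients with at least one SAE".

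**The definitions.** Protocol X.1 counts a harmful manifestation as an adverse event "regardless of whether or not the manifestation is related to the study". Seriousness rests on outcome criteria such as death, threat to life, admission or prolonged stay. Relatedness is not required.

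**The recording.** Protocol X.2 has the study doctor record adverse events from consent through the whole participation, on the adverse events page of the case report form. Protocol VIII.2 lists the items that close the eCRF. One is "Non-serious adverse events (AEs"), and another is "Outside planning, an SAE module".

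**The SAE form.** Protocol X.3 states: "Only SAEs directly related to the additional procedures required for this study are to be reported to the sponsor immediately". It exempts events from the natural course of the disease, from treatments given as usual care, and any other event unrelated to the added procedures. The form appears in that same section: "The investigator will fill in the serious adverse event report form (from the study case report form") and sends it to the sponsor's vigilance unit.

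**The SAP data items.** SAP 7.1.1 takes into account any adverse event that a patient reports or that is recorded at a visit. For each it lists intensity, treatment, duration and causality. Seriousness is not on the list.

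**The concern.** A test on patients with at least one SAE needs a record that marks events as serious by the same rule in both arms. The only place described for serious events is the SAE module or form, and the only stated trigger for completing that form is relatedness to study-added procedures. Most serious events after a knee arthroplasty can be expected to come from the surgery or from other illness, which X.3 places among the events that need not be reported to the sponsor.

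Two things are at stake. The SAE table could be nearly empty, and so say nothing about readmissions, prolonged stays or other serious complications. Ascertainment could also differ by arm, because the exercise sessions and the self-exercise programme exist only in the intervention arm, and exercise is the only study procedure for which X.2 names adverse events.

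**Working it through.** The documents give no SAE rate, expected count or power, so there is no figure of the plan's to reproduce. The check is mainly textual.

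**Step 1. Follow one event through the rules.** Take a readmission for a surgical complication, judged unrelated to any study procedure. It could occur in either arm.

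| Place | What happens to the event |
|---|---|
| Protocol X.1 | It is an adverse event and it is serious. Cause is irrelevant. |
| Protocol X.2 | It should go on the adverse events page. |
| Protocol VIII.2 | The listed adverse event item is for non-serious events. Serious ones have a separate module with no stated entry rule. |
| Protocol X.3 | It need not be reported to the sponsor. The SAE form is described only for the reporting route. |
| SAP 7.1.1 | If recorded, it carries intensity and causality but no seriousness item. |
| SAP 7.1.2 | It should count in the SAE test. |

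Three outcomes are compatible with the text:

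- It is entered in the SAE module and counted.
- It is entered on the adverse events page without a flag. It then counts in the test on any AE or SAE but not in the SAE test, unless someone classifies it afterwards.
- It is entered in neither and is lost to both tests.

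Nothing in the documents fixes which of these applies. Intensity cannot stand in for seriousness: mild, moderate or severe is a different scale from the X.1 criteria.

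**Step 2. Now take a serious event attributed to an exercise session.** X.3 requires immediate reporting, so the SAE form is completed and the event is identifiable. This path is open only in the intervention arm. Controls also undergo study-added procedures (the preoperative assessment, the daily D1 to D5 assessment, the questionnaires), so the reporting trigger is not empty for them.

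**Step 3. What incomplete capture would do to the test.** The inputs are:

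- Arm size: "150 patients are planned to be enrolled in the experimental group (multidisciplinary programme) and 150 patients in the control group" (protocol IV.3), so n = 150 per arm.
- Level: SAP 4.1 says "The tests used will be bilateral with a significance threshold of 2.5% for the two primary endpoints and 5% for the secondary endpoints". It names no level for safety tests, so two-sided 5% is assumed.
- True SAE rate q, equal in both arms: assumed 5%, 10% or 15%.
- Captured fractions c_I (intervention) and c_C (control): assumed.

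The recorded rates are q·c_I and q·c_C. The rejection probability is the sum over all pairs (i, j) of Bin(i; 150, q·c_I) × Bin(j; 150, q·c_C), taken where the two-sided Fisher p-value is below 0.05.

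| c_I / c_C | q = 5% | q = 10% | q = 15% |
|---|---|---|---|
| 1 / 1 | 2.4% | 3.3% | 3.4% |
| 1 / 0.5 | 11.9% | 29.8% | 48.1% |
| 0.5 / 0.25 | 3.8% | 11.9% | 20.6% |
| 0.2 / 0 | 0.4% | 8.2% | 29.6% |

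Equal and full capture keeps the test below its level. Unequal capture mostly does not, although with few recorded events (low q and low capture) the rejection rate stays below 5%.

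**Step 4. The near-empty case.** X.2 and X.3 expect no SAE from the study procedures. If only related SAEs were identifiable, the expected table would be close to 0 v 0. At an assumed q of 10% it would omit about 0.10 × 150 = 15 serious events per arm. That result would be uninformative rather than biased.

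**The case against.** The strongest reply is that notifying the sponsor and recording in the case report form are different duties. X.3 restricts the first. X.1 and X.2 govern the second and set no limit by arm, cause or seriousness. Adverse events are collected in both arms preoperatively, at discharge and at months 3, 6 and 12 (protocol VII.3). SAP 7.1.1 admits any reported or recorded event and has a causality class for unrelated ones, which would be pointless if only related events entered. The SAE module in VIII.2 carries no stated restriction, and X.3 asks for a causality opinion on each SAE. SAP section 8 also values pathology-related admissions for each patient.

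Much of this stands. A reader might infer that the Fisher test rests on notified SAEs only, that control-arm SAEs can hardly be counted, and that the comparison is biased against the programme. The documents do not support that. The SAP never names notified SAEs as its source, recording is meant to cover both arms, and some study-added procedures also apply to controls. With no related SAE expected, a near-empty table is as plausible as a lopsided one.

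The reply does not settle how an unrelated serious event is to be identified as serious. X.2 points to a page, VIII.2 labels the matching item as non-serious, and SAP 7.1.1 has no seriousness item. The Annex 12 vigilance grid, legible only in the earlier protocol copy but carrying the same file label in the latest one, says that non-notifiable events may be collected in the case report form. That is permission, not a requirement, and is supporting evidence only.

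**Conclusion.** The concern holds as a gap in specification. Followed as written, the protocol and SAP do not guarantee that a serious event unrelated to study procedures is recorded and flagged as serious, by the same rule, in both arms. The SAE comparison could therefore be incomplete and possibly unequally ascertained.

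Unequal capture, and its direction, is a risk left open rather than something the documents show. The rejection rates above, such as 29.8% against 3.3% at q = 10%, rest on assumed SAE rates, assumed capture fractions and an assumed 5% level. They show the sensitivity of the test, not its expected behaviour in this trial. The efficacy endpoints are unaffected. What changes is what the safety comparison can conclude, and the correction is a cheap improvement.

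**What to change.** Reconcile protocol VIII.2, X.2 and X.3 with SAP 7.1.1 and 7.1.2:

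- State in protocol VIII.2 and X.2 that every event meeting the X.1 definition of serious is entered in the eCRF, in both arms, from consent to month 12, whatever its cause.
- Add a seriousness item to the adverse event record and to the list in SAP 7.1.1.
- State in SAP 7.1.2 that the Fisher test on SAEs uses this all-cause eCRF record.
- Leave the rules on notifying the sponsor in X.3 as they are, and say there that they do not limit eCRF entry.

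The cost is some wording, one added field and a few more eCRF entries.

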## **8 Health economics analysis**

The EQ-5D scores will be converted into utilities based on French value tables. The utilities imputed for the periods corresponding to the interval between 2 collections will be multiplied by the corresponding durations to obtain QALYs. The differences in QALYs will be compared between the two groups.

The intervention will be valued on a flat-rate basis based on the time spent by the professionals as described in the protocol and by multiplying the estimated cost of each session by the proportion of patients having undergone the sessions.

Hospital admissions related to the pathology (imputed during the end-of-study meeting) will be valued based on 1) ENCC (French national hospital costs study database) costs and 2) rates. The costs will be estimated for each patient and the average costs in each arm will be compared using non-parametric tests.

The incremental cost-utility ratio will be calculated by comparing the difference in average costs with the difference in average QALYs, with a bootstrap sensitivity analysis.

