### **4. Health economics evaluation**

This is a prospective study in which resource consumption by the patients in each arm will be collected in the case report form and evaluated 1) from the Health Insurance perspective, based on the reference nomenclature and prices in force at the end of the study, and 2) from the care-system perspective using the available hospital accounting data.

The resources collected include:

- time period before the intervention by the surgeons in the control group, and by the teams in charge of education and rehabilitation management in the intervention group;
- length of hospital stay and GHM (or the components of the medical unit summary) corresponding to the stay for the intervention;
- length of stay at rehabilitation care facilities;
- consultations and nursing or physiotherapy procedures during the follow-up period;
- imaging studies and medications consumed during follow-up;
- length of time off work or the time taken to resume normal activity.

There are, a priori, no structure costs related to the intervention as this uses existing capacities. However, we can consider designing a budgetary impact and an impact in terms of therapeutic education professionals if this intervention was to be widely used.

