### **Health economics evaluation.**

The intervention costs (from the Health Insurance perspective for the basic calculation) will be compared. In the event that the most expensive strategy is the one which provides the best functional outcome and quality of life, we will carry out a cost-effectiveness analysis. The values will be taken from the EuroQol questionnaire. The base ratio estimation will be completed with a sensitivity analysis (particularly on the pricing of education procedures) and a bootstrap estimation of confidence intervals.

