## **6.3 Quality of life**

### **6.3.1 Definition**

Quality of life is assessed using the MOS SF-12 and EQ-5D scales.

For the SF-12, the physical (PCS) and mental (MCS) health scores will be calculated at the enrolment visit, preoperative visit, month 3, month 6 and month 12.

The EQ-5D is collected at the enrolment visit and at months 6 and 12; it will be used for the health economics analysis.

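### The planned cost test need not test the mean cost difference used in the cost-utility ratio, and QALYs are compared without adjusting for the enrolment EQ-5D utility

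*Supplement*

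**What the plan says.** SAP section 8 (Health economics analysis) sets out three comparisons.

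- **Costs:** "The costs will be estimated for each patient and the average costs in each arm will be compared using non-parametric tests". No test is named.
- **QALYs:** utilities for the intervals between EQ-5D collections "will be multiplied by the corresponding durations to obtain QALYs". Then: "The differences in QALYs will be compared between the two groups". No covariate is mentioned.
- **Ratio:** obtained by "comparing the difference in average costs with the difference in average QALYs, with a bootstrap sensitivity analysis". The protocol, in the health economics part of IX.4, likewise plans "a bootstrap estimation of confidence intervals".

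A baseline utility is available. SAP 6.3.1 states: "The EQ-5D is collected at the enrolment visit and at months 6 and 12". The intervention is costed at a flat rate, as session cost times the proportion attending. Admissions are valued once at national cost-study values and once at tariff rates.

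On time, the protocol (II.2) compares costs at 6 and 12 months. SAP 8 does not repeat this, and it does not say whether the clock for costs and QALYs starts at enrolment or at surgery.

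**The concern.** A cost-utility ratio is a statement about arithmetic means. A test of the cost difference helps the reader only if it addresses the same quantity. A rank test asks whether costs in one arm tend to exceed those in the other. With skewed costs, or with a constant added to one arm, that can differ from the question about means, so the report could show a significant cost difference beside a mean difference near zero, or the reverse.

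For QALYs, the next EQ-5D after enrolment is at month 6, so the enrolment utility carries much of the weight in the total. SAP 6.1.2, 6.2.2, 6.3.2 and 6.4.2 deal with baseline for pain, personalised WOMAC, SF-12 and steps by constrained longitudinal analysis. The utility, which feeds the ratio, gets no corresponding treatment. What is lost is precision, in an estimate whose plausible effects are small.

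A further, secondary issue is that the time over which QALYs accrue differs between patients and is not fixed by the SAP.

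**Working it through.** **Inputs from the documents.** 150 patients per arm (protocol IV.3). EQ-5D at enrolment, month 6 and month 12 (SAP 6.3.1). Follow-up of 14 to 15 months (protocol summary). Secondary tests two-sided at 5% (SAP 4.1).

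**Assumptions not in the documents.** Utility SD 0.20 to 0.30 (0.25 for the precision calculation), correlation 0.5 between utilities, all cost distributions, and a flat intervention cost of 400.

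**Plan's own figure.** Enrolment to programme is 0 to 1 month, programme to surgery is 2 months at the stated minimum, and follow-up after surgery is 12 months. The sum is 14 to 15 months, as stated. Time from enrolment to surgery is therefore 2 to 3 months on the plan's figures, although the 2-month minimum has no upper limit.

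**1. Cost test, if it is a rank test.** Simulated at 150 per arm, showing the share of trials rejecting at 5%:

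| Scenario | Mann-Whitney | Welch t |
|---|---|---|
| Equal means, lognormal, log-SD 0.5 v 0.7 | 38% | 5% |
| Equal means, log-SD 0.5 v 0.9 | 90% | 6% |
| Equal medians, means about 10,200 v 13,500 | 6% | 77% |
| Tied tariff plus flat 400 in one arm, equal means (two cases) | 94%, 100% | 5%, 4% |
| No ties, flat 400, equal means, similar shape | 6% | 5% |

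The tied case shows the mechanism. Suppose 70% of controls sit at a base tariff and 30% have extra costs, while in the intervention arm everyone carries the flat 400 and 24.1% have extra costs, which makes the means equal. The chance that an intervention patient costs more than a control is about 0.70 + 0.30 × 0.241 × 0.5 = 0.74. A rank test sees 0.74 against 0.50; the mean difference is 0. The last row shows that the discrepancy is small when the shapes are alike and there are no ties.

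**2. Baseline utility in the QALY.** With trapezoids starting at enrolment, the weight of the enrolment utility is (wait + 6)/24 years: (2 + 6)/24 = 0.333 to (3 + 6)/24 = 0.375.

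The standard error of a chance baseline difference is SD × √(2/150): 0.20 × 0.1155 = 0.023 and 0.30 × 0.1155 = 0.035.

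Contribution to the QALY difference at one standard error: 0.023 × 0.333 = 0.008 to 0.035 × 0.375 = 0.013. If the enrolment utility were instead carried forward to month 6, its weight would double and so would these figures.

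**3. Precision gained by adjusting.** Take SD 0.25, correlation 0.5 and a wait of 2.5 months. The weights are 0.354 (enrolment), 0.604 (month 6) and 0.25 (month 12).

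- Unadjusted variance per patient: 0.0625 × [0.354² + 0.604² + 0.25² + (0.354 × 0.604 + 0.354 × 0.25 + 0.604 × 0.25)] = 0.0625 × 1.006 = 0.063. SE = √0.063 × 0.1155 = 0.029.
- Given enrolment utility: 0.0625 × [0.75 × (0.604² + 0.25²) + 2 × 0.25 × 0.604 × 0.25] = 0.0625 × 0.396 = 0.025. SE = √0.025 × 0.1155 = 0.018.

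Simulation gave the same two standard errors. The type I error of the unadjusted comparison was 5.5%, so it is valid but less precise.

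**4. Horizon.** One extra pre-operative month, with no effect on health, adds utility/12: 0.4/12 = 0.033 to 0.6/12 = 0.050 QALY. With a simulated one-month difference between arms, the unadjusted test rejected in 39% of trials and the baseline-adjusted test in 77%. Baseline adjustment therefore does not solve this.

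**The case against.** SAP 8 does not say rank test. A bootstrap or permutation test of means is also non-parametric, and the sentence itself speaks of averages. This stands: the rank reading is an inference. It is a reasonable one, because the protocol's only other use of the term (IX.4, primary endpoint analysis) is for Mann-Whitney, and SAP 8 mentions the bootstrap separately, for the ratio. Even on that reading, only the cost p-value is affected. The ratio is mean-based and has its own bootstrap.

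A reader might infer that the QALY difference is biased or spurious. The documents do not support that. Enrolment EQ-5D is collected and can enter the QALY, and under randomisation the unadjusted difference is unbiased with about nominal type I error. Chance imbalance is ordinary sampling error.

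A reader might also infer that longer waits in the intervention arm will inflate its QALYs. Surgery is scheduled before randomisation, both arms have the same stated follow-up, and no difference in time to surgery is shown. On the 14 to 15 month figures, a one-month mean difference would need one arm entirely at the minimum and the other at the maximum. Some drift is possible, since only the intervention arm must fit sessions in at least two months ahead and no maximum is set.

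Finally, SAP 8 names only sessions and admissions as costs, while protocol IX.4 also lists items such as "length of stay at rehabilitation care facilities", outpatient care and time off work. It would be too strong to say those items are dropped: SAP 8 does not withdraw the protocol's list.

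**Conclusion.** The point holds as a mismatch and a loss of precision in a secondary analysis. It does not touch either primary endpoint.

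- **Cost test:** not named. Read as a rank test, it does not test the mean difference in the ratio. The disagreement ranges from negligible to near-certain rejection at equal means, depending on skew, ties and the flat-rate cost, all of which are assumed here.
- **QALYs:** no baseline adjustment is stated. The estimate is unbiased, but a one-standard-error baseline imbalance moves it by about 0.008 to 0.013 QALY (SD 0.20 to 0.30, trapezoid from enrolment). Under the assumptions in step 3, adjustment lowers its standard error from about 0.029 to 0.018. The documents give no cost difference or threshold, so the effect on a decision cannot be stated.
- **Horizon:** secondary and conditional. Each month of difference between arms would be worth 0.033 to 0.050 QALY at an assumed utility of 0.4 to 0.6.

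**What to change.** In SAP 8:

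1. Replace the unnamed tests by the difference in arithmetic mean costs with a bootstrap confidence interval, taken from the same resamples as the ratio.
2. Estimate incremental QALYs by linear regression on arm, enrolment EQ-5D utility and centre, refitted in each resample so that the numerator and denominator of the ratio come from the same patients.
3. State one start point and one fixed horizon for both costs and QALYs, and how the utility of each interval is formed (trapezoid or carried forward). Reconcile this with the protocol's 6- and 12-month cost comparison. If the clock starts at surgery, say how the pre-operative programme cost enters.

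The cost is SAP wording and modest extra analysis. The enrolment utility is already collected, so no new data are needed.
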